### Study data

Data on low-value practices, mortality, complications, unplanned readmissions, ICU and hospital length of stay, and missed injuries will be extracted from the provincial trauma registry, used successfully in recent work [36]. Data collection is mandatory for all transfers and/or admissions with a primary diagnosis of injury in all provincial trauma centers [66]. Chart data are extracted in each center using coding protocols and are centralized at the Ministry of Health where they are submitted to data quality protocols. Supervision by a data manager, on-going training, an electronic forum, and quarterly meetings with stakeholders are used to ensure data quality. A recent re-abstraction of a random sample of 80 patient charts stratified by injury type and severity suggested 98% concordance on fields used for A&F (unpublished data).

### Process evaluation

We will assess fidelity, reach, and contextual factors using *Medical Research Council guidance on process evaluation of complex interventions *[67]. To assess fidelity, we will monitor the ability to deliver the multifaceted intervention and simple A&F as intended. The research team member delivering the intervention will document whether intervention components were delivered as planned and describe the challenges encountered. We will also evaluate the download of educational materials (e.g., case revision tool, clinical decision rules, shared decision-making tools) using Google Analytics [68] and examine submitted action plans to document whether they address feedback and describe strategies to facilitate de-implementation based on a local assessment of barriers and facilitators [69]. To assess reach, we will conduct 20 individual interviews (recommended sample size for informational redundancy) [70] with medical directors and trauma program managers in 20 participating centers (10 in each arm, stratified by designation level), 1 to 2 months before the end of each evaluation cycle (Fig. 1, Additional file 3: Table S3). They will be asked about strategies used to disseminate feedback to clinicians involved in trauma care, challenges in implementing the action plan, and unintended consequences of the intervention (e.g., difficulty planning transfer management without scans). We will also evaluate contextual influences on feedback responses, including elements within (e.g., competing priorities, support and commitment of decision makers, available resources) and outside the trauma center (e.g., national initiatives, policies, discussions with clinicians in other centers) [67]. Finally, at the end of the trial (months 27 to 30; Fig. 1, Additional file 3: Table S3), we will conduct 20 individual interviews (10 in each arm) with clinicians working in participating centers (stratified by designation level) to determine their recall and understanding of feedback received and the actions taken to change the practices in their organization. These clinicians will be identified through trauma program managers who will not be given any information about the purpose of the interviews to minimize selection bias. We will strive for an equal representation of males and females and of clinicians with different clinical experiences and disciplines for interviews.

### Sample size calculations

As all level I–III trauma centers will participate in this trial, we calculated the statistical power to detect a minimum important difference with a fixed number of clusters and patients per cluster (Additional file 3: Table S6). All sample size parameter values were accurately estimated by historical data from four 18-month observation periods between April 1, 2017, and March 31, 2020, using trauma registry data from the 30 level I–III trauma centers in the *Québec Trauma Care Continuum *[36]. Based on stakeholder input, a 25% relative difference in the primary outcome (proportion of patients with low-value initial diagnostic imaging) would be considered a minimum important difference. With 15 clusters in arm 1 and 15 clusters in arm 2 and an average of 285 patients per cluster period in a parallel arm cRCT with a baseline observation period, we will achieve 90% power to detect a 25% relative difference between the intervention and control arms (0.14 in the control arm versus 0.105 in the intervention arm) at a two-sided 5% level of significance [71]. We assumed a within-period intra-cluster correlation coefficient of 0.044, and a cluster autocorrelation coefficient of 0.984 (correlation from before to after). Given that the median observed absolute difference for interventions targeting de-implementation in the most recent meta-analysis on the topic was 10.5% [12], an absolute difference of 3.5% is considered plausible. For our secondary outcomes, we will have 90% power to detect absolute differences of 7.4% and 16.0% in neurosurgical consultation and repeat imaging for transfers, respectively [71].

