### Randomization, allocation, blinding, and adherence

Centers will be randomized to simple A&F (control) or the multifaceted intervention (intervention) in a 1:1 ratio. An independent statistician at the Ottawa Methods Center (outside of the province in which the trial will be conducted and fully independent from the sites) will generate the allocation sequence using the covariate-constrained allocation technique [64] to ensure that study arms are balanced for designation level (I/II and III), cluster size, and the pre-intervention measure of the primary outcome. The allocation sequence will only be revealed on trial initiation. An independent INESSS professional will allocate centers to their randomization group. Local trauma committees will not be told explicitly what aspect of the intervention is randomized; they will only be aware that there are two variations of the intervention. Data extractors and data analysts will be blinded to group allocation. Due to the nature of the intervention, it will not be possible to blind the investigators to allocation groups. To minimize non-adherence and contamination, only participants in the intervention arm will participate in the refinement phase. We do not envisage major problems with adherence because quality assurance activities are mandatory in line with designation requirements [43].

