### Data analysis plan

All statistical analyses will be based on an intention-to-treat principle and will be conducted by a statistician blinded to group assignment. Analysis of the primary outcome will be conducted at the individual patient level using weighted independence estimating equations with robust standard errors to provide valid statistical inference for the cluster-average target estimand [72]. A small sample correction will be applied to control for the small number of clusters [73]. To produce the intervention effect as a relative risk with a 95% confidence interval, we will use modified robust Poisson regression for clustered data [74]. To obtain correct type I error rates, variables used in the covariate-constrained allocation will be included as covariates (volume, designation level, and baseline proportion), and to improve power and precision [75], the analysis will adjust for prespecified patient risk factors: age, comorbidities, and injury severity (anatomical and physiological parameters). Secondary outcomes measured as binary variables will be analyzed using a similar approach. Secondary outcomes measured as continuous variables (i.e., ICU and hospital length of stay) will be analyzed using linear regression after log transformation. To address the secondary objective of evaluating trends over time, we will model repeated outcomes over 6-month intervals and include time and group-by-time interactions. We will use least square mean differences between the arms to determine whether outcomes have changed over time [76]. There are missing data on covariables in the registry, which will be handled with multiple imputation, shown to lead to accurate effect estimates for trauma quality indicators in simulations [77–79].

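### The stated 90% power matches a calculation with equal-sized centres; it should be restated for the planned cluster-average analysis, whose precision depends on the harmonic mean centre size

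*Protocol article*

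**What the plan says.** The section on sample size calculations states "we will achieve 90% power to detect a 25% relative difference between the intervention and control arms", with proportions of "0.14 in the control arm versus 0.105 in the intervention arm", tested "at a two-sided 5% level of significance". The size input is "With 15 clusters in arm 1 and 15 clusters in arm 2 and an average of 285 patients per cluster period", in a parallel design with a baseline period. The within-period intra-cluster correlation is 0.044 and the cluster autocorrelation 0.984, both taken from registry data on the same 30 centres. The article gives no CV, range or harmonic mean of centre size. It refers to Table S6 of Additional file 3, which is not shown.

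The data analysis plan specifies "weighted independence estimating equations with robust standard errors to provide valid statistical inference for the cluster-average target estimand", with a small-sample correction. It adjusts for the allocation variables (volume, designation level, baseline proportion) and for patient risk factors.

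Two places show that centres differ in size. The setting section lists 3 level I, 5 level II and 22 level III centres, from specialised urban hospitals to small-town hospitals. The randomization section requires arms to be "balanced for designation level (I/II and III), cluster size, and the pre-intervention measure of the primary outcome".

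**The concern.** Under a cluster-average estimand every centre counts equally, whatever its number of patients. The sampling error of the treatment effect then depends on the mean of 1/m over centres, that is, on the harmonic mean size and not on the arithmetic mean. Whenever sizes differ, the harmonic mean is the smaller of the two.

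In many cluster trials this hardly matters, because the between-centre term dominates. Here the autocorrelation of 0.984 means that baseline adjustment removes nearly all of that term. What remains is mostly within-centre sampling error, which scales with 1/m.

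The article does not link its power figure to this weighting or to the small-sample correction. If the true figure is materially below 90%, a null result would be read as stronger evidence against a 25% reduction than it is.

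**Working it through.** **Inputs from the article.** p1 = 0.14, p2 = 0.105, difference d = 0.035; K = 15 centres per arm; m = 285 per centre-period; ρ = 0.044; cluster autocorrelation c = 0.984; two-sided α = 0.05.

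**Inputs assumed here.** The CV and shape of the centre-size distribution, and 28 degrees of freedom (30 centres minus 2) for the t reference.

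**Step 1: reproduce the 90% with equal centres.**
- Design effect without baseline: 1 + 284 × 0.044 = 13.496.
- Before-after correlation of centre proportions: r = 285 × 0.044 × 0.984 / 13.496 = 0.9143.
- Difference-in-differences (DID): 13.496 × 2(1 − r) = 2.313, so effective n per arm = 4275 / 2.313 = 1848.
- ANCOVA on baseline: 13.496 × (1 − r²) = 2.214, so effective n per arm = 4275 / 2.214 = 1931.
- Variance sum: 0.14 × 0.86 + 0.105 × 0.895 = 0.2144.
- DID: z = 0.035 / √(0.2144/1848) = 3.25, power 0.901. ANCOVA: z = 3.32, power 0.913.
- With t on 28 degrees of freedom: 0.880 and 0.894.

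The stated 90% therefore follows from the stated inputs with every centre at 285.

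**Step 2: how much of the variance depends on size.** After baseline differencing, the per-centre variance is proportional to ρ(1 − c) + (1 − ρ)/m = 0.0007 + 0.0034. About 83% of it is the term in 1/m.

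**Step 3: unequal centres, equal weight per centre.** Replace 1/m by the mean of 1/m over centres. For lognormal sizes with mean 285 this is (1 + CV²)/285. Put V = ρ + (1 − ρ) × mean(1/m). The variance factor is 2(V − ρc) for DID and V − (ρc)²/V for ANCOVA, and z = 0.035 / √(0.2144 × factor / 15).

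Example at CV 0.5: mean(1/m) = 1.25/285 (harmonic mean 228) and V = 0.04819. The DID factor is 2(0.04819 − 0.04330) = 0.00979, so z = 2.96 and power is 0.841. The ANCOVA factor is 0.00930, so z = 3.04 and power is 0.859.

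| Assumed CV | Harmonic mean | DID / ANCOVA, normal | DID / ANCOVA, t(28) |
|---|---|---|---|
| 0 | 285 | 0.901 / 0.913 | 0.880 / 0.894 |
| 0.2 | 274 | 0.892 / 0.905 | 0.870 / 0.884 |
| 0.3 | 262 | 0.880 / 0.894 | 0.857 / 0.872 |
| 0.5 | 228 | 0.841 / 0.859 | 0.815 / 0.834 |
| 0.7 | 191 | 0.783 / 0.806 | 0.754 / 0.778 |
| 1.0 | 143 | 0.672 / 0.705 | 0.641 / 0.674 |

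With a normal reference, power stays at 0.90 up to a CV of about 0.08 (DID) or 0.25 (ANCOVA). It falls below 0.80 at about 0.65 or 0.72.

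**Step 4: a two-tier illustration.** Take 4 level I/II and 11 level III centres per arm, with mean 285. If the larger centres are 2 times the size of the smaller, power is 0.878/0.893. At 3 times (558 against 186, CV 0.58) it is 0.838/0.857. At 4 times (633 against 158, CV 0.74) it is 0.795/0.817. The ratios are assumptions.

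**Step 5: the weighting is the cause.** For DID with a normal reference, variance-efficient weights give 0.888 at CV 0.6 and 0.869 at CV 1.0. Size weights give 0.884 and 0.851. Equal centre weights give 0.814 and 0.672.

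**The case against.** Several points on the other side stand.

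- The 90% is right on its stated inputs, so there is no arithmetic error. Nor is it tied strictly to equal sizes: ANCOVA with a normal reference holds 0.90 up to a CV of about 0.25.
- The CV is not in the article, and the lognormal shape is a second assumption. The two-tier illustration loses somewhat less: ANCOVA power is 0.857 at CV 0.58, against 0.835 for lognormal sizes at CV 0.6.
- The primary denominator is low-risk patients. Level III centres transfer most of their major trauma, so differences in total volume need not carry over in full to this denominator. Use of size in the allocation shows that it varies, not by how much.
- Patient-covariate adjustment is planned partly to gain precision, and the calculation above does not credit it. As an illustration only, an assumed 15% cut in residual variance at CV 0.5 would raise the ANCOVA z from 3.04 to 3.04/√0.85 = 3.29 and power to 0.909. The article gives no such figure and claims no such gain in its power statement.
- Table S6 and the cited method may say how size variation was handled.

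A reader might infer that the authors ignored unequal sizes, or that the trial is shown to be underpowered. The article supports neither: the first cannot be judged without Table S6, and the second needs the CV. It would also be wrong to say that the power belongs to a different design, since clusters, periods and effect are the same and only the weighting and reference distribution differ.

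That efficient weighting loses little is true, but the data analysis plan did not choose it.

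**Conclusion.** The point holds as a mismatch between the power figure and the planned analysis. The article's 90% equals an equal-size calculation, while the analysis weights centres equally and applies a small-sample correction. Given that sizes differ and that 285 is an arithmetic mean, the size effect on power is downward; only its amount is open. It runs from about 1 point at CV 0.2 to 21 to 23 points at CV 1.0 with a normal reference. A t reference on 28 degrees of freedom takes a further 2 to 3 points and puts both versions below 0.90 even with equal centres. These figures rest on the assumed CV, the lognormal shape, the 28 degrees of freedom and no credit for patient covariates. The secondary-outcome power could not be checked, because the article does not give its inputs.

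**What to change.** Recompute the primary-outcome power from the 30 observed centre-period counts of eligible low-risk patients, or from their harmonic mean, using cluster-average weights and a t reference that matches the small-sample correction. Replace the 90% by that figure and report the CV or harmonic mean beside it. If a gain from patient covariates is to be credited, estimate it from the same historical data and state it. Check the power statements for neurosurgical consultation (7.4% absolute difference) and repeat imaging (16.0%) in the same way.

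The cost is one rerun with registry data already used for the other sample size parameters. All level I–III centres already take part, so no patients or centres are added, and the planned analysis does not change. The only downside is that the stated power will probably be lower.

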### Data analysis plan

All statistical analyses will be based on an intention-to-treat principle and will be conducted by a statistician blinded to group assignment. Analysis of the primary outcome will be conducted at the individual patient level using weighted independence estimating equations with robust standard errors to provide valid statistical inference for the cluster-average target estimand [72]. A small sample correction will be applied to control for the small number of clusters [73]. To produce the intervention effect as a relative risk with a 95% confidence interval, we will use modified robust Poisson regression for clustered data [74]. To obtain correct type I error rates, variables used in the covariate-constrained allocation will be included as covariates (volume, designation level, and baseline proportion), and to improve power and precision [75], the analysis will adjust for prespecified patient risk factors: age, comorbidities, and injury severity (anatomical and physiological parameters). Secondary outcomes measured as binary variables will be analyzed using a similar approach. Secondary outcomes measured as continuous variables (i.e., ICU and hospital length of stay) will be analyzed using linear regression after log transformation. To address the secondary objective of evaluating trends over time, we will model repeated outcomes over 6-month intervals and include time and group-by-time interactions. We will use least square mean differences between the arms to determine whether outcomes have changed over time [76]. There are missing data on covariables in the registry, which will be handled with multiple imputation, shown to lead to accurate effect estimates for trauma quality indicators in simulations [77–79].

We will synthesize qualitative data from transcribed focus groups and individual interviews through thematic analysis [80] using QDA miner software (Provalis Research, Montréal, Canada) [81]. We chose thematic analysis because it allows for data organization and reduction, which facilitates a comprehensible description and interpretation of relevant elements [82]. To ensure credibility and reliability, peer debriefing will be carried out by experienced researchers at different analysis stages [83, 84]. We will ensure transferability using purposive sampling to maximize the chances of obtaining information that is relevant to the research objectives [83]. Credibility and trustworthiness will be reinforced by involving a coder in qualitative data analysis with no knowledge of the subject and by independent validation of the entire data analysis by a member of the research team [80]. We will use descriptive statistics to report on the sex and gender, experience, and discipline of participants and to assess intervention fidelity. To assess adherence and contamination, we will analyze process data for external influences and the use of implementation strategies in control centers. We will triangulate data on intervention effectiveness and process evaluation using a joint display to explain findings (i.e., why the intervention was effective or not) [58, 85, 86].

Effectiveness data will only be analyzed at the end of the trial. Process evaluation data collected at the end of the first cycle will be analyzed to inform intervention refinements for the second cycle, and data collected at the end of the trial will be used to refine the intervention prior to upscaling.

#### Subgroup analyses

We have planned subgroup analyses by designation level, baseline proportion of low-value initial imaging, patient sex (information on patient gender is not available), and patient age for effectiveness; and by clinician gender, age, years in practice, and discipline for the refinement of intervention and for process evaluation.

#### Sensitivity analysis

If contamination is present, we will use an instrumental variable adjustment method [87] in sensitivity analyses. To evaluate the influence of non-adherence, we will conduct per-protocol analyses. To assess the influence of multiple imputation, we will conduct complete case analyses. Fine and Grey models will be used to assess the influence of competing risks of mortality for analyses on hospital and ICU length of stay.

### Economic evaluation

We are currently conducting an early economic evaluation examining the potential benefit of the multifaceted intervention, which has informed intervention development. This includes a systematic review of the cost-effectiveness of A&F interventions [15], a budget impact analysis of low-value practices and a simulation-based early economic evaluation to estimate the potential cost-effectiveness of a hypothetical multifaceted intervention targeting low-value trauma care (initial results suggest the intervention is always dominant). Following the trial, we will update the simulation model with trial data to evaluate the cost-effectiveness of the true intervention. The economic evaluation will be conducted according to Canadian Agency Guidelines for Economic Evaluation of Health Technologies [88] and results will be reported according to the Consolidated Health Economic Evaluation Reporting Standards 2022 statement [89].

### Trial management

The main coordinating center will be at the CHU de Québec—Université Laval Research Center. Patient-level data from the trauma registry is hosted at the Ministry of Health and Social Services, and an extraction of this database with no patient-identifiable information will be accessed by the trial analyst (blinded to group allocation) through a password-protected portal at *INESSS* offices. Qualitative data from intervention refinement and process evaluations will be kept in password-protected computers in locked offices at the CHU de Québec-UL research center. Our trial coordinator will work with an *INESSS* professional to coordinate trial initiation and recruitment/randomization, implement the intervention, and obtain trauma registry data. They will also be responsible for liaising with trauma program managers in each center and coordinating the collection of qualitative data for the process evaluation. The trial steering committee, co-led by the two principal investigators [name], includes a representative of *INESSS* [name], trauma medical directors of the three regional trauma committees [name], patient partners [name] and equity, diversity, and inclusion champions [name]. The committee will oversee trial conduct and knowledge translation activities and ensure we meet project deliverables according to timelines. A data monitoring committee will not be used as data for effectiveness analysis is not collected within the trial and the risk to participants is considered very low. Any trial modifications will be submitted to the trial steering committee for approval, recorded in our registered protocol, and reported in final manuscripts.

### Stakeholder, patient, and public involvement

Our primary stakeholder partner is the provincial paragovernmental organization responsible for overseeing healthcare quality (INESSS). Our research team has been working in collaboration with this organization since 2010. They have been involved in designing the trial so it can be embedded in their 2023 evaluation cycle, and they will be involved in all phases of trial conduct. The trial has also been designed in collaboration with the *Trauma Association of Canada* (association of clinicians involved in trauma care across Canada) and *Health Services Organisation* (responsible for hospital accreditation programs in Canada). The design of this cRCT has also been informed by national research collaboratives, the *Canadian Traumatic brain injury Research Consortium* and the *Canadian Critical Care Trials Group*, and national knowledge translation networks, *Choosing Wisely Canada*, and the *A&F Metalab*. To ensure trial results are relevant to other high-income countries with similar trauma care infrastructures, we have partnered with the UK *Trauma Audit Research Network* and *Victoria State Trauma Outcomes Registry and Monitoring group*in Australia. Three patients [name] with varying injury profiles were integrated in the consensus process to select low-value practices targeted in this trial [52]. We first conducted a preparatory meeting to explore their perceptions on low-value trauma care, establish their priorities, and prepare for their integration. Patient perceptions and priorities were presented by a patient at the consensus meeting. All patients participated in the meeting and voted on practices to be retained. Patients will not be involved in intervention refinement as they are not end users [90]. However, two patients [name] are on the trial steering committee. No members of the general public are involved.

